### Questionnaire Design

2.4

The questionnaire, which is given to the patients, consists of two core parts:
A.Sociodemographic and Clinical Characteristic questionnaire: This part of the questionnaire will aim to know the target population in a more detailed way. This section consists of two parts: (1) sociodemographic characteristics, such as age, gender, level of education, marital status, occupation, and income; (2) clinical characteristics, such as type of disease, heart failure classification (in case of heart failure), type of cancer, metastasis (in case of cancer), type of referral (inpatient or outpatient), length of hospitalization, and comorbidities.B.FACIT‐Pal Quality of Life Questionnaire: The psychometric properties of this instrument were assessed in 2009 by Lyons et al. [27] via a randomized clinical trial study. The FACIT instrument is known as a comprehensive instrument for measuring the quality of life of patients with chronic diseases, which includes 27 items from the FACT‐G questionnaire and the palliative care subscale (FACIT‐Pal).

In the study by Lyons et al. [27], the psychometric properties of the 46‐item FACIT‐Pal were examined in English. The 19 items—which are specifically about palliative care—were developed based on interviews conducted with patients with advanced cancer. After adding the palliative care section and examining the internal reliability with Cronbach's alpha coefficient, the palliative care section of this questionnaire obtained a Cronbach's alpha of 0.82 and in general, the Cronbach's alpha of the other domains of the English questionnaire obtained a Cronbach's alpha between 0.75 and 0.93. This questionnaire includes a total of 46 items, which are scored on a 5‐point Likert scale. The options for these questions are scored on a 5‐point Likert scale ranging from 0 to 4, and the respondent will receive a total score between 0 and 184. Higher scores indicate a higher quality of life score [27, 36]. In the present study, the FACIT‐Pal questionnaire will be translated into Persian based on the implementation of FACIT's methodology.

### Sampling Process

2.5

Among the individuals with cancer and heart failure referred to the inpatient wards and heart failure and cancer outpatient clinics of the IKHC, 552 patients will be selected as the research sample by the convenience sampling method, based on inclusion and exclusion criteria. Of the desired sample size, 50% will be allocated to patients with heart failure (276 patients) and 50% to patients with cancer (276 patients). The necessary matters regarding the study process, the objectives of the research, as well as the confidentiality of their information, will be explained to the patients, and they will be invited to participate in the present study if they wish. Written informed consent will be obtained, and the research instruments, including the demographic questionnaire and the FACIT‐Pal questionnaire, translated into Persian, will be provided. Patients will be asked to complete the questionnaire using a self‐report approach.

### Sample Size

2.6

It is suggested to include 5 to 10 subjects per item for psychometric assessment studies [47]. According to this recommendation, it was decided to include 10 patients for each item on the 46‐item FACIT‐Pal questionnaire, resulting in a total requirement of 460 patients to achieve the maximum sample size. After considering a 20 percent attrition rate, the final sample size is determined to be 552 patients (276 diagnosed with heart failure and 276 diagnosed with cancer).

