##### Participants

2.3.1.1

The study sample will be divided into two groups: (1) Patients with heart failure, comprising 50 percent (276 patients) of the total sample size, will be recruited from CCU, cardiology wards, and the heart failure clinic of IKHC; and (2) Patients with cancer: comprising 50 percent (276 patients) of the total sample size, will be recruited from the cancer institute (oncology ward) of IKHC and the cancer clinics of IKHC. The inclusion criteria will be: (1) consent to participate in the study; (2) diagnosed with heart failure or cancer; (3) 18 years of age or older; (4) having the literacy to read and write in Persian. The exclusion criteria will be: (1) presence of a documented, untreated severe psychological disorder recorded in the medical record by a psychiatrist or treating physician, including schizophrenia spectrum disorders, bipolar disorder, or active substance use disorder, which is considered to cause significant functional impairment, defined as impaired judgment, cognition, or communication that interferes with the individual's capacity to understand study procedures or complete study assessments; (2) uncorrected communication impairments (auditory, visual, or verbal) that preclude participation; and (3) completion of less than 80% of the study measures.

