#### Psychometric Assessment

2.6.1

Following the translation process, internal consistency reliability of the instrument will be examined by the computation of Cronbach's alpha and McDonald's omega coefficients. These coefficients will be computed in SPSS software and will be interpreted as weak for estimates of ~ 0.5, needs revision for estimates between 0.5 and 0.7, and adequate for estimates at 0.7 or higher.

To examine the evidence of the structural validity of the instrument, covariance‐based confirmatory factor analysis (CFA) will be implemented using software such as the lavaan package in R or covariance‐based modeling routines in SmartPLS. To assess the goodness of fit of the measurement model, a number of commonly used fit indices [48] will be used including RSMEA (good fit < 0.06), SRMR (good fit ~ < 0.08), CFI, GFI, AGFI, and TLI (good fit ~ > 0.9). Known‐groups validity will be examined by comparing FACIT‐Pal scores by disease stage within patient groups (i.e., Heart failure classification and metastatic status will be obtained from medical records and verified with clinician approval) using ANOVA.

Reliability coefficients will be computed overall and examined separately for cancer and heart failure subgroups. Measurement invariance [48] between cancer and heart failure patients will be examined with multiple‐group analyses, sequentially fitting and comparing CFA model fit for (1) configural invariance (i.e., the same factor structure is imposed on both patient groups), (2) weak invariance (i.e., the factor loadings are constrained to be equal across the patient groups), and (3) strong invariance (i.e., the factor loadings and intercepts are constrained to be equal across the patient groups).

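### The 20% attrition allowance is added to 460 instead of dividing by 0.80, so 552 patients leave about 442, some 18 short of the stated requirement (minor)

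*Protocol article*

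**What the plan says.** The sample size in section 2.6 (Sample Size) of the protocol article rests on a subjects-per-item rule and not on a power calculation. The rule is stated as "It is suggested to include 5 to 10 subjects per item for psychometric assessment studies". The authors take its upper end: "it was decided to include 10 patients for each item on the 46‐item FACIT‐Pal questionnaire". From this they derive a required total of 460. They then allow for loss: "After considering a 20 percent attrition rate, the final sample size is determined to be 552 patients", split as "276 diagnosed with heart failure and 276 diagnosed with cancer". Sections 2.3.1.1 (Participants) and 2.5 (Sampling Process) repeat the 276 + 276 split.

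The Participants section also lists "completion of less than 80% of the study measures" as an exclusion. This can be known only once a patient has been given the questionnaire, so it is one way in which recruited patients drop out of the analysis.

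Section 2.6.1 (Psychometric Assessment) plans some analyses by disease: "Reliability coefficients will be computed overall and examined separately for cancer and heart failure subgroups". It also plans multiple-group factor models to test measurement invariance between cancer and heart failure.

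**The concern.** An attrition rate is the fraction of recruited patients who do not reach the analysis. To end with a required number after such a loss, one divides that number by one minus the rate. Multiplying it by one plus the rate gives too small a figure, and the gap grows with the rate. The stated 552 equals 460 × 1.20 exactly, which points to the second calculation.

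At stake is the one property that section 2.6 claims for the design: that 460 patients, 10 per item, remain after 20% are lost. A reader would take that property as secured, and the section's own inputs do not secure it.

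**Working it through.** **Inputs, all from section 2.6:** 46 items; 10 patients per item; 20% attrition; final size 552, split 276 and 276; cited range 5 to 10 per item.

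**1. Reproduce the stated figures.**
- Requirement: 46 × 10 = 460, as stated.
- Inflation by multiplying: 460 × 1.20 = 552, an exact match.
- Inflation by dividing: 460 / (1 − 0.20) = 575, no match. It is 23 patients (23/552 = 4.2%) higher, too far apart for rounding to explain.

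**2. What 552 leaves at the stated attrition.**
- Analysable patients: 552 × 0.80 = 441.6, about 442.
- Shortfall: 460 − 441.6 = 18.4, about 18 patients; 18.4/460 = 4.0%.
- Per item: 441.6/46 = 9.6, against the chosen 10.

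**3. The attrition that 552 can absorb.**
- 1 − 460/552 = 92/552 = 16.7%.

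| Attrition | Remaining of 552 | Per item |
|---|---|---|
| 10% (illustrative) | 496.8 | 10.8 |
| 15% (illustrative) | 469.2 | 10.2 |
| 16.7% (break-even) | 460 | 10.0 |
| 20% (stated) | 441.6 | 9.6 |

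**4. The number that delivers 460 at 20%.**
- 460/0.80 = 575; with two equal groups, 576 (288 each).
- Check: 576 × 0.80 = 460.8, which is 10.0 per item.

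**5. Context: the by-disease analyses.**
- Per group before loss: 276/46 = 6.0 per item.
- Per group after 20% loss: 276 × 0.80 = 220.8, about 221; 220.8/46 = 4.8 per item.
- With the correct inflation: 288 × 0.80 = 230.4; 230.4/46 = 5.0 per item.

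Correcting the inflation therefore moves the group ratio only from 4.8 to 5.0. The ratio is low mainly because the size was set on the total.

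**The case against.** **The shortfall changes little.** The rule gives a range, and the plan took its upper end; the lower end would need only 5 × 46 = 230 patients. At 9.6 per item the study is still near the top of that range, and no estimate or test has been identified whose conclusion would differ between 442 and 460 patients. This stands, and it is why the point is minor.

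**A 20% loss may not occur.** The study is a single cross-sectional self-report without follow-up, and any loss up to 16.7% leaves 460 or more. That is true, but 20% is the protocol's own assumption, and the claim has to hold under it.

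**552 might already be net of loss.** Section 2.5 says that the 552 are selected on the inclusion and exclusion criteria, and incomplete response is listed as an exclusion. One could infer that incomplete responders are replaced and do not count. The text does not say so. The abstract describes 552 as the number invited, and section 2.6 presents 552 as the figure after the attrition allowance has been made. If replacement is intended, no inflation was needed to begin with.

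**A stronger reading of the disease groups.** A reader might infer from 4.8 per item that the by-disease reliability and invariance analyses fall below the protocol's own minimum of 5. The document does not support that:
- It applies the rule to the whole study and derives a total; no per-group requirement appears.
- It does not say that every by-disease model uses all 46 items at once.
- At the weak and strong invariance steps, loadings and then intercepts are held equal across groups, so those parameters draw on patients from both. Dividing one group by 46 does not describe the information available there.
- The inflation error contributes only the step from 5.0 to 4.8.

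The group figures are worth knowing, but they are not a breach.

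**Conclusion.** The point holds as a minor arithmetic correction. Section 2.6 states a requirement of 460 and a 20% attrition rate, and 552 does not satisfy both: about 442 patients remain, 18 (4%) too few, at 9.6 per item in place of 10.

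This rests on two assumptions: that the 20% is a share of those recruited, which is the ordinary meaning of an attrition rate, and that lost patients are not replaced, since the article mentions no replacement. If the authors meant 20% as a mark-up on 460, the allowance corresponds to 16.7% attrition and should be described that way.

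The error does not take the study outside the range that it cites, and it gives no ground for redesigning the factor analyses. The figures of about 221 patients and 4.8 per item in each disease group are context for reading the by-disease results.

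**What to change.** Restate the last sentence of section 2.6, for example: *552 recruited allows for 16.7% attrition; at 20% attrition about 442 patients are analysable (9.6 per item, still within the cited range of 5 to 10).* This costs one sentence and makes the stated ratio slightly less favourable.

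If the authors prefer to keep 460 analysable patients at 20% attrition, the target becomes 575, or 576 with 288 per disease group. That is 24 more patients than planned, and the abstract and sections 2.3.1.1, 2.5 and 2.6 would all need the new number.

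Optionally, add that the by-disease analyses would rest on about 221 patients per group at 20% attrition. No change to the planned analyses is needed.

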#### Psychometric Assessment

2.6.1

Following the translation process, internal consistency reliability of the instrument will be examined by the computation of Cronbach's alpha and McDonald's omega coefficients. These coefficients will be computed in SPSS software and will be interpreted as weak for estimates of ~ 0.5, needs revision for estimates between 0.5 and 0.7, and adequate for estimates at 0.7 or higher.

To examine the evidence of the structural validity of the instrument, covariance‐based confirmatory factor analysis (CFA) will be implemented using software such as the lavaan package in R or covariance‐based modeling routines in SmartPLS. To assess the goodness of fit of the measurement model, a number of commonly used fit indices [48] will be used including RSMEA (good fit < 0.06), SRMR (good fit ~ < 0.08), CFI, GFI, AGFI, and TLI (good fit ~ > 0.9). Known‐groups validity will be examined by comparing FACIT‐Pal scores by disease stage within patient groups (i.e., Heart failure classification and metastatic status will be obtained from medical records and verified with clinician approval) using ANOVA.

Reliability coefficients will be computed overall and examined separately for cancer and heart failure subgroups. Measurement invariance [48] between cancer and heart failure patients will be examined with multiple‐group analyses, sequentially fitting and comparing CFA model fit for (1) configural invariance (i.e., the same factor structure is imposed on both patient groups), (2) weak invariance (i.e., the factor loadings are constrained to be equal across the patient groups), and (3) strong invariance (i.e., the factor loadings and intercepts are constrained to be equal across the patient groups).

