Palliative care, as an approach aimed to alleviate pain and suffering among patients with chronic diseases, can be applied to patients and their families. Ultimately, it seeks to optimize the quality of life for patients and their families [18]. While much research has focused on palliative care for patients with cancer, patients with heart failure also require high‐quality palliative care due to the significant burden of their disease [19]. In the Primary Health Care (PHC) system in Iran, palliative care is not highlighted adequately and is counted as a novel approach to terminally and/or chronically ill patients [20, 21]. The WHO introduces palliative care as an effective strategy to enhance quality of life among individuals with cancer and their families, as it can ease about 90 percent of physical, psychological, and spiritual distress [9]. On the other hand, the American Heart Association (AHA) has pinpointed applying palliative care besides usual care [22]. Bagheri et al. suggest future research focus on core elements of palliative care, such as quality of life [23].

As mentioned above, a primary goal in palliative care is to optimize patients’ quality of life. Thus, in order to measure the effectiveness of palliative interventions, the presence of an accurate, valid, and reliable scale is crucial. Over the past decades, the assessment of quality of life has gained significance to ensure that clinical and care‐related decisions align with patients’ perspectives [24]. In a systematic review, the absence of a comprehensive quality‐of‐life measurement for Iranian patients with cancer has already been reported [25]. One of the most recent questionnaires validated in Iran is the “Minnesota Living with Heart Failure Questionnaire (MLHF‐Q)”. This questionnaire is specifically produced to evaluate the quality of life among the individuals suffering from heart failure. This questionnaire measures patients’ physical, mental, and social conditions using 21 items [26]. However, it is specific to individuals with heart failure and generalizing it to other chronic conditions needs more investigations. Moreover, the FACIT‐Pal (in comparison with the MLHF‐Q) evaluates the quality of life of general chronic illness in palliative care patients. It focuses on Physical well‐being, Social well‐being, Emotional well‐being, and Functional well‐being, and palliative‐specific items [27].

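### One 0.9 limit for GFI and AGFI conflicts with the RMSEA limit beside it: with 46 items, most of the RMSEA range called good misses 0.9 under the usual ML definition

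*Protocol article*

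**What the plan says.** Section 2.6.1 (Psychometric Assessment) plans a covariance-based CFA in lavaan or SmartPLS. It lists six fit indices with a benchmark for each: RMSEA below 0.06 ("will be used including RSMEA (good fit"), SRMR below about 0.08, and a single value of about 0.9 for the remaining four ("CFI, GFI, AGFI, and TLI (good fit"). The benchmarks make no allowance for the number of items or patients. The section names no estimator, and it does not say that all six must pass or what happens when they disagree.

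The same section plans a cancer versus heart-failure invariance analysis by "sequentially fitting and comparing CFA model fit" through configural, weak and strong steps.

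On size, Questionnaire Design states "This questionnaire includes a total of 46 items". Sample Size (2.6) derives the number of patients from it: "resulting in a total requirement of 460 patients to achieve the maximum sample size", raised to 552 for attrition, with "276 diagnosed with heart failure and 276 diagnosed with cancer".

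**The concern.** CFI and TLI compare the model with a baseline model. GFI and AGFI in their usual form are built from the raw discrepancy between observed and fitted covariances. That discrepancy includes sampling error, which accumulates over every degree of freedom. With 46 items there are many degrees of freedom, so both indices are pulled down even when the model is right. A value of 0.9 therefore does not mean the same thing for them as for CFI and TLI.

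CFA is the only construct-validity method named in the abstract. If two of its six benchmarks respond mainly to questionnaire length and sample size, a sound Persian version could be described as fitting poorly on those two, or modified needlessly, for reasons unrelated to the translation.

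**Working it through.** **Inputs from the protocol article.** Items p = 46 (Questionnaire Design). Five domains (Background: four well-being domains plus the palliative items). 460 analysable and 552 recruited patients, 276 per disease (Sample Size). Limits from 2.6.1.

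**The plan's own figure.** 46 × 10 = 460; 460 × 1.2 = 552; 552 / 2 = 276. This reproduces. A true 20% loss from 552 leaves 552 × 0.8 = 442, or 221 per group, so 442 to 552 pooled and 221 to 276 per group span the plausible sizes.

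**Assumptions.** The documents do not fix the factor model or the estimator. I take five correlated factors and normal-theory ML, with GFI and AGFI computed on the covariance structure.

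- Moments: 46 × 47 / 2 = 1081.
- Parameters: 46 loadings + 46 residual variances + 10 factor correlations = 102.
- df = 1081 − 102 = 979. This does not depend on how the items are divided among domains.

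**Formulas.** F = df × (RMSEA² + 1/(N−1)); GFI ≈ p/(p + 2F); AGFI = 1 − (1081/979) × (1 − GFI).

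**Where 0.9 is crossed.**

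- GFI = 0.9 requires F = 46 × (1/0.9 − 1)/2 = 2.556.
- AGFI = 0.9 requires GFI = 1 − 0.1 × 979/1081 = 0.9094, so F = 2.290.
- Solving RMSEA = √(F/979 − 1/(N−1)) gives:

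| Pooled N | GFI > 0.9 needs RMSEA below | AGFI > 0.9 needs RMSEA below |
|---|---|---|
| 460 | 0.021 | 0.013 |
| 552 | 0.028 | 0.023 |

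The plan's limit is 0.06. At N = 460 GFI therefore agrees with RMSEA over only 0.021/0.06 = 35% of the range called good. At N = 552 the share is 0.028/0.06 = 47%.

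**At the RMSEA limit itself (0.06).**

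- N = 460: F = 979 × (0.0036 + 1/459) = 5.657; GFI = 46/57.31 = 0.803; AGFI = 0.782.
- N = 552: GFI 0.813, AGFI 0.793.
- N infinite: F = 3.524; GFI = 46/53.05 = 0.867; AGFI = 0.853. More patients do not remove the conflict.

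**Correct model (RMSEA = 0).**

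| N | Expected GFI | Expected AGFI |
|---|---|---|
| 221 | 0.838 | 0.821 |
| 230 | 0.843 | 0.827 |
| 276 | 0.866 | 0.852 |
| 442 | 0.912 | 0.903 |
| 460 | 0.915 | 0.906 |
| 552 | 0.928 | 0.921 |

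A correct model needs about N = 384 for an expected GFI of 0.9 and about N = 428 for AGFI.

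**Simulation check (ML fits of a five-factor, 46-item CFA, 20 to 60 replicates per setting).**

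- Mild misfit, N = 460: mean RMSEA 0.037, SRMR 0.041, CFI 0.929 and TLI 0.925, all good by the plan, with GFI 0.860 and AGFI 0.845. No replicate reached 0.9 on either (largest GFI 0.872).
- Mild misfit, N = 552: RMSEA 0.038, GFI 0.864, AGFI 0.850; again none reached 0.9.
- Correct model, pooled: GFI passed in every replicate at N = 460 and 552. AGFI passed in 90% at 460 and in all at 552.
- Correct model at N = 230 and 276: no replicate reached 0.9 on either index, with loadings from 0.3–0.7 to 0.7–0.9 and with five-category items. The largest GFI was 0.854 and 0.879.

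**Sensitivity.** A second-order (df 984) or one-factor (df 989) structure moves the expected values by about 0.002 or less. The definition of GFI matters far more. For a correct model, a ULS-type GFI was about 0.96 at both group sizes. An ML GFI with item means in its denominator was about 0.90 (N = 230) to 0.92 (N = 276).

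**The case against.** The strongest reply is that there is no decision rule here to break. The plan lists customary indices with approximate benchmarks, does not ask for all of them to pass, and attaches no verdict to GFI or AGFI. In the simulated example four of the six indices support the model, and several indices are reported precisely because they can disagree. A reader might infer that a sound scale would be declared a poor fit. The text does not support that, and this part of the reply stands.

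A reader might also infer that every disease-specific model must fail. That does not follow either. The article announces no separate CFA by disease, only a multiple-group sequence judged by comparing successive models, and it does not say that 0.9 applies to each group. The group-level shortfall also depends on the definition of GFI. The invariance steps constrain intercepts, which brings in a mean structure, and a GFI that includes item means can reach 0.9 at those sizes.

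Nor is it true that any model with RMSEA below 0.06 misses 0.9 in the pooled sample: a correct or nearly correct one passes.

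What the reply does not remove is that one sentence gives benchmarks that disagree over most of the range one of them calls good. Leaving the weighing of indices to a fuller analysis plan would be ordinary, but the 0.9 value for GFI and AGFI is stated here. Because the estimator and software are open, the same data could fall on either side of it according to how GFI is computed.

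**Conclusion.** The concern holds as a poorly chosen benchmark. With the usual ML covariance-structure indices and an assumed five-factor model, misfit that the plan itself calls good on RMSEA puts pooled GFI and AGFI below 0.9 over most of that range, by up to about 0.10 for GFI and 0.12 for AGFI at N = 460. At the size of one disease group (N = 221 to 276) even a correct model is expected to give GFI 0.84 to 0.87 and AGFI 0.82 to 0.85. That matters only if the limit is applied group by group, and it does not carry over to a ULS-type GFI or one that includes item means.

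The consequence is discordant readings on two of six indices, with no stated way to resolve them, so the judgement of fit could be made after seeing the data. Sample size, scores, reliability and known-groups comparisons are unaffected.

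**What to change.** In 2.6.1, remove the cut-offs for GFI and AGFI and judge fit on RMSEA with its 90% confidence interval, SRMR, CFI and TLI. If GFI and AGFI are wanted for comparison with other translations, report them descriptively without a threshold, and name the estimator so that the reader knows which GFI is meant.

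This alters one sentence, needs no further data or patients, and should be made before the CFA is run. The small cost is less direct comparability with any validation that used the 0.9 limit, which descriptive reporting largely recovers.

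### Naming Welch's ANOVA for the known-groups comparison would be a cheap safeguard, because stage group sizes are uncontrolled and score spread may differ between stages

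*Protocol article*

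**What the plan says.** Section 2.6.1 (Psychometric Assessment) examines known-groups validity by comparing "scores by disease stage within patient groups". The stage variables are heart failure classification and metastatic status, and the method is given as "metastatic status will be obtained from medical records and verified with clinician approval) using ANOVA". It names no variance option, no check of equal variances, no significance level and no pass/fail rule for this comparison.

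Section 2.5 (Sampling Process) states that "552 patients will be selected as the research sample by the convenience sampling method". Section 2.6 (Sample Size) fixes the split by disease only: "276 diagnosed with heart failure and 276 diagnosed with cancer". No quota by stage is given. Section 2.4 (Questionnaire Design) describes the total: "the respondent will receive a total score between 0 and 184". The article gives no SD by stage and no expected stage distribution.

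**The concern.** The usual ANOVA F-test estimates one variance from all groups together, and the larger groups dominate that estimate. If the smaller group is the more variable, the pooled standard error is too small and the test rejects too often. If the smaller group is the less variable, the pooled standard error is too large and the test rejects too seldom, with a loss of power. For metastatic status, with two groups, ANOVA is the pooled-variance t-test and behaves in the same way.

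Equal group sizes largely protect against this, but the sampling plan does nothing to secure them. The comparison also carries some weight. It is the only planned analysis in the article that sets the score against a measure of clinical severity. A liberal test could overstate known-groups validity, and a conservative one could miss a real difference between stages.

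**Working it through.** **The plan's own figure.** 46 items × 10 = 460, and 460 × 1.20 = 552, or 276 per disease. This reproduces the stated total. It comes from an items-per-subject rule and was not derived for the stage comparison, so the plan has no figure for that test to reproduce.

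**Inputs.**
- From the documents: N = 276 per disease as recruited, and 460 / 2 = 230 per disease before the attrition allowance.
- Assumed, because not stated: nominal level 5%; two metastatic groups; four heart failure classes; stage splits of 50:50, 30:70 and 10:90; SD ratios of 1, 1.25 and 1.5; normal scores.

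**Closed form for two groups.** Let the smaller group have size n1 and SD s1, and the larger n2 and s2.
- Pooled variance: sp² = [(n1 − 1)s1² + (n2 − 1)s2²] / (n1 + n2 − 2)
- Standard error used by ANOVA: √[sp²(1/n1 + 1/n2)]
- True standard error: √(s1²/n1 + s2²/n2)
- With r = used / true, the actual type I error is about 2[1 − Φ(1.96 r)].

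*30:70 (83/193), smaller group 1.5 times as variable.* sp² = (82 × 2.25 + 192 × 1) / 274 = 1.374. Used standard error = √(1.374 × 0.01723) = 0.154. True standard error = √(2.25/83 + 1/193) = 0.180. r = 0.856 and 1.96 r = 1.68, so the type I error is about 9.3%.

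*The same split, larger group 1.5 times as variable.* sp² = (82 × 1 + 192 × 2.25) / 274 = 1.876. Used 0.180, true 0.154, r = 1.168 and 1.96 r = 2.29, so about 2.2%.

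*10:90 (28/248), smaller group 1.5 times as variable.* sp² = (27 × 2.25 + 247 × 1) / 274 = 1.123. Used 0.211, true 0.291, r = 0.727 and 1.96 r = 1.43, so about 15.4%. Reversed, r = 1.374 and 1.96 r = 2.69, so about 0.7%.

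**Simulation** (equal true means, 200,000 replicates per scenario, N = 276). Type I error of the pooled test:

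| Split | SD ratio | Smaller group more variable | Larger group more variable |
|---|---|---|---|
| 30:70 | 1.25 | 7.2% | 3.3% |
| 30:70 | 1.5 | 9.4% | 2.3% |
| 10:90 | 1.25 | 10.1% | 1.9% |
| 10:90 | 1.5 | 15.4% | 0.7% |

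At 50:50 the pooled test gives 5.0% to 5.1% at every SD ratio up to 2. With equal SDs it gives 4.9% to 5.1% at any group sizes. The Welch test gives 4.9% to 5.2% in all scenarios, and N = 230 gives nearly the same values.

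**Four classes** (assumed sizes 14/69/110/83, SDs running from 1 to 1.5 across classes): 8.9% when the smallest class is the most variable and 3.3% when it is the least. With four equal groups of 69 the pooled test gives 5.3% for that SD range, and 5.8% to 5.9% if the SDs run from 1 to 2.

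**Cost of Welch when variances are equal** (largest true gap 0.5 SD):
- 50:50 and 30:70: 0 to 0.2 points of power.
- 10:90: 62.0% against 59.3% at N = 230 (2.7 points), and 70.4% against 68.2% at N = 276 (2.2 points).
- Four groups: 0.5 to 2.3 points.

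**The case against.** The strongest reply is that the article fixes nothing wrongly. It says ANOVA, which does not exclude a Welch version, and an article commonly leaves the variance option to an analysis plan that is not shown here. That stands as a reason not to call this an error. It does not remove the improvement: the method is named in print, its unqualified meaning is the pooled test, and naming Welch removes the doubt.

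The second reply is that the harm depends on unequal SDs, which the documents neither report nor imply. This also stands. Convenience sampling leaves group sizes open, but it does not make spreads unequal.

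Several stronger readings are tempting, and the documents do not support them:
- A reader might infer from the upper bound of 184 that less ill patients bunch near the top. No ceiling effect is reported, the scale is also bounded at 0, and recruitment is from the CCU, wards and clinics of a tertiary centre. Neither the presence nor the direction of unequal spread can be inferred.
- A reader might infer that the validity conclusion will be wrong twice as often as claimed. No significance level or decision rule is attached to this comparison, so the 5% is a convention assumed here.
- A reader might infer that this is the score's only link to anything outside the questionnaire. Measurement invariance is also tested across diagnosis. That analysis asks whether the items behave alike in the two diseases, not whether the score tracks severity, so the narrower statement holds and the wider one does not.
- A reader might take Welch to be free. It costs up to about 3 points of power when variances are equal and one group is small.

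**Conclusion.** This is a cheap, optional improvement and not an error in the plan. What the documents establish is that ANOVA is named and that stage sizes are uncontrolled. Whether the pooled test is distorted depends on an assumption about spread that they cannot settle. Under SD ratios of 1.25 to 1.5, its type I error is about 7-9% or 2-3% for a 30:70 split and about 10-15% or 1-2% for a 10:90 split, against a nominal 5%. With equal SDs it is correct, and with equal group sizes it is correct or nearly so. Welch stays close to 5% throughout at a small power cost, which makes it the better default when neither the stage mix nor the spreads are known in advance.

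**What to change.** In section 2.6.1, replace the reference to ANOVA with Welch's ANOVA for heart failure class and a Welch t-test for metastatic status, or with heteroscedasticity-robust standard errors in whatever model compares the stages. Report the mean differences with 95% intervals from the same method, together with the size and SD of each stage group.

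The cost is one phrase in the analysis text. It needs no new data or patients. The power downside is the 0 to 3 points shown above. Making the change before data are seen also avoids choosing the test after looking at the variances.
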